## **8. REGULATORY ISSUES**

## **8.1. ETHICS APPROVAL**

The Study Coordination Centre has obtained approval from the Bradford and Leeds Research Ethics Committee (REC) and Health Research Authority (HRA). The study must also receive confirmation of capacity and capability from each participating NHS Trust before accepting participants into the study or any research activity is carried out. The study will be conducted in accordance with the recommendations for physicians involved in research on human subjects adopted by the 18th World Medical Assembly, Helsinki 1964 and later revisions.

## **8.2. CONSENT**

### Participants Able to Consent

Consent to enter the study will be sought from each participant (patients, family members/friends and critical care nurses) only after a full explanation has been given, an information leaflet offered, and time allowed for consideration. A signed participant consent must be obtained before their enrolment into the study. The right of the participant to refuse to participate without giving reasons must be respected by the research team. All participants are free to withdraw at any time from the protocol treatment without giving reasons and without prejudicing further treatment. They will be made aware that their participation in the study will not affect their care or employment in any way. The study team will deal with consenting as an ongoing process and, before any study tasks take place, participants will be asked if they are happy to remain in the study. The research team will also ensure that participant's wishes are documented on medical notes and the clinical team is aware of the study team's plan of action.

### Participants Unable to Consent

A participant is deemed unable to decide whether to take part in research if they cannot:

- Understand the information relevant to the decision (information should be given in a way that is appropriate to the particular participant)
- Retain that information for long enough to conclude the decision (this may be for a relatively short time, but still long enough to enable decision-making to occur)
- Use or weigh that information as part of the process of making the decision (participants need to understand the consequences of each option).
- Communicate their decision (whether by talking, using sign language or any other means).

Due to the specificity of the care group, patient's mental capacity is expected to fluctuate throughout the study and if so, a personal consultee will be included to decide whether patients should continue taking part in the research study. A Patient Regaining Capacity Consent Form should be signed post-operatively when possible, ideally before participants resume with the study in ICU, and after periods of lacking capacity.

Decisions whether or not the participants have the capacity to give consent will be made by the PI or a Senior Researcher, who has appropriate training and experience in assessing consent. The PI has been formally trained on how to obtain informed consent from participants and aware of the Mental Capacity Act 2005.

### **8.3. CONFIDENTIALITY**

The CI and all members of the delegated study team will preserve the confidentiality of participants taking part in the study. All data will be collected and managed in line with the Data Protection Act 2018 and GDPR.

The risk of confidentiality breach will be minimised by ensuring all study-related data is stored securely in a pseudonymised form and participants will be identified by a study ID number only. Any patient-identifiable data that is shared with parties outside of the research study team will be modified such that it is in a linked anonymised form (with removal of patient hospital number, NHS number, name, date of birth, etc.). Additionally, the research team will ensure that any patient-identifiable data is safely kept in a key-locked cabinet only accessible to members of the study team and remaining study documentation is always securely stored in a password protected computer and/or research office.

### **8.4. DATA STORAGE AND MANAGEMENT OF DATA**

The research team will follow the principles of Good Clinical Practice (GCP), the EU GDPR and UK Data Protection Act 2018 to ensure all the data collected will be anonymised and the confidentiality of all participants will be protected. We do not anticipate any safety concerns associated with this study, for either participants or the researchers involved.

Patient demographics and meta-data will be recorded for all patients. All pre- and post-screened data collected will be kept on an ICHT NHS computer and be password protected. Only members of the study delegation log will have access to these electronic files. Original consent forms will be kept in the ISF and one copy will be uploaded in the patients' electronic notes. The ISF will be kept with the CI, in a key-locked cabinet inside a key/password-locked office accessible only to members of the research team who have signed the delegation log.

This study involves the collection of questionnaires, participant's pictures and the use of audio-visual recording devices with patients, family members/friends and healthcare professionals, which requires ethical approval. All responses to questionnaires and interviews will be pseudonymised to ensure confidentiality. This will be done by assigning a study ID number to all participants enrolling into the research study, which will be used for the questionnaires and to address participants during the interview. The use of a study ID number will then be used throughout the study and data analysis. The research team will also create single participant's study folders, which will contain individualised anonymised data collected during the study (e.g., questionnaires, nurses' checklists, etc.). Participant's folders will be retained in the key-protected research offices, only accessible by members of the study team. Additionally, the study team will delete participants contact details after concluding the study data collection and results shared with consented participants.

Interviews will be recorded with an encrypted audio-recording device provided by ICHT and videos with a study video-camera that will be kept in a key locked cabinet inside the CI's office. All interview data and electronic transcripts (when transcribed by a member of the research team) will be stored securely on an encrypted and secure institutional password protected ICHT computer. Interview recordings will be deleted as soon as the transcription has been completed and analysed by the research team. Video will be recorded either with a video-recorder device that belongs to the study team or self-recorded by family member/friends at home.

Subsequently, videos and pictures will be sent to the PI's encrypted NHS email and then safely uploaded to a study password protected iPad and into a digital photo frame, respectively. All video recordings and pictures will be deleted from the devices as soon as the individual participant's intervention is finished and at ICU discharge. All videos stored in the study team's video-recorded device will be deleted after the intervention is finished or upon ICU discharge. No family video and/or personal pictures digital copies will be retained by the study team without participant's prior consent.

All published data will be pseudonymised, including any direct quotations we may include to illustrate key themes. Files containing any identifiable information will only be available to the PI and appropriate members of the study team on the delegation log. These files will be password-protected and kept separately from files where only the unique study ID is used.

### Study closure

Following data analysis, dissemination and study closure, the research team will retain essential documents until notified by the Sponsor (ICHT) and then archived for at least ten years after study completion, as per ICHT policy. Participant's study files and other source data (including copies of protocol, PIS, records of informed consent, and other documents pertaining to the conduct of the study) must be kept for the maximum period of time permitted by the institution.

Documents should be stored in such a way that they can be accessed/data retrieved at a later date. Consideration should be given to security and environmental risks. No study document will be destroyed without prior written agreement between the Sponsor and the research team. Should the research team wish to assign the study records to another party or move them to another location, a prior written agreement must be obtained from the Sponsor.

### Reducing bias

All interviews will be carried out by the same researcher throughout the study to reduce differences in the way questions are asked and will be audio recorded and transcribed verbatim prior to analysis. Recruitment of participants and analysis will be carried out simultaneously allowing for constant comparison and the identification of similarities. Any data gathered will be then analysed using a framework approach.

It is essential to acknowledge that the PI will be carrying out interviews and is currently a supporting member of the direct care team. The PI has access to patient records through various electronic systems and will be using these records as a means to pre-screen prior to the approaching and enrolment of potential participants. Although clinicians can very effectively use transferable skills from clinical interviewing to interviewing for research purposes, the blurring of the two roles could potentially present an ethical bias. While the primary researcher is conducting this study, the PI will assume the responsibility to not provide direct care to any participants involved in the project. The PI will also aim to be as transparent as possible regarding the clinical position as a critical care researcher, throughout the study process, including interviewing, analysis of the results and dissemination of the findings. Data analysis will be conducted by the primary researcher, and emerging themes will be further discussed with the CI and SIs.

## **8.5. INDEMNITY**

The Sponsor, Imperial College Healthcare NHS Trust, holds a standard NHS hospital indemnity and insurance cover with NHS Resolution for NHS Trusts in England, which apply to this study.

## **8.6. SPONSOR**

Imperial College Healthcare NHS Trust (ICHT) will act as the main Sponsor for this study. Delegated responsibilities will be assigned to the NHS trusts taking part in this study.

## **8.7. FUNDING**

This research study is being undertaken as part of a Pre-Doctoral Research Fellowship that has been awarded to the PI, [name], by the IHC and is being funded by the NIHR Imperial BRC.

We currently do not have funding to support the participation of patient, family members and healthcare professionals. Additionally, other members of the research team will not receive any money contributions from supporting this study.

## **8.8. AUDITS**

The study may be subject to audit by ICHT under their remit as sponsor and other regulatory bodies to ensure adherence to GCP and the UK Policy Framework for Health and Social Care Research. The Sponsor may also carry out audits to ensure compliance with the protocol and appropriate local regulations.

Direct access will be granted to authorised representatives from the Sponsor/Host institution (ICHT), the partner institution (Imperial College of London) and the regulatory authorities to permit trial-related monitoring, audits and inspections.

# **9. STUDY MANAGEMENT**

### Daily Study Management

The day-to-day management of the study will be co-ordinated from Hammersmith Hospital by the PI. The CI will assume the responsibility to supervise the PI throughout the study and discussion about the study management will occur during weekly meetings. Study data management and analysis will be also discussed with SIs at a later stage of the research study.

### Protocol Amendments

Every care was taken when drafting this study protocol, but corrections or amendments may be necessary. These will be circulated to investigators in the study prior to re-submission. Problems relating to this study should be referred, in the first instance, to the Chief Investigator

No amendments to this protocol will be made without prior consultation and agreement with the Sponsor. Any amendments to the study that appear necessary during the study must be

discussed with the Research Team and the Sponsor concurrently. If agreement is reached concerning the need for an amendment, it will be produced in writing by the PI and will be made a formal part of the protocol following ethical and regulatory approval.

The research team is responsible for ensuring that any substantial amendments to an approved study protocol, are not to be initiated without previous NHS REC review/approval and not until the REC's approval letter has been obtained by the research team.

### Protocol Deviations

Any protocol deviations will be documented in a protocol deviation form and safely filed in the ISF. The CI and SIs will be made aware of the protocol deviation. Corrective and preventative actions will be discussed and implemented to prevent new deviations to the study protocol.

### Study Reports

Study outcomes will be regularly reported by the PI to the CI and SI and further discussed during monthly meetings. Two different reports will be sent to the Imperial Health Charity to declare any study mid-year and end of study progress with the aim to ensure their continuum support in the research study.

The Sponsor and REC will be also sent an annual/end of study report upon request and will be informed about study closure, within the required timelines.

## **10. PUBLICATION POLICY**

The PI will co-ordinate dissemination of data from this study and ensure all published/presented data will be pseudonymised. All publications (e.g., manuscripts, abstracts, oral/slide presentations, book chapters) based on this study will be reviewed by each sub-investigator prior to submission. All communication concerning the study, including at a conference or seminar, shall acknowledge the responsible parties and the invaluable Imperial Health Charity financial contribution to the study.

## **APPENDICES/ANNEXES**

- ANNEX I – Schedule of Assessments (SoA)
- ANNEX II – PIS for Patients
- ANNEX III – ICF for Patients
- ANNEX IV – PIS for Family Members/Friends
- ANNEX V – ICF for Family Members/Friends
- ANNEX VI – PIS for Critical Care Nurses
- ANNEX VII – ICF for Critical Care Nurses
- ANNEX VIII – ICF for Patient Regaining Capacity Consent Form
- ANNEX IX – Draft Invitation Email to Participants, Family Members/Friends and Nurses
- ANNEX X – GP Letter for Participants
- ANNEX XI – Participant’s pre-operative pathway and intervention delivery diagram
- ANNEX XII – Critical Care Nurse’s checklist
- ANNEX XIII – Video Guided Script Template for Family Members/Friends
- ANNEX XIV – Participant’s post-ICU discharge and follow-up pathway
- ANNEX XV - PIS for Personal Consultees
- ANNEX XVI – ICF for Personal Consultees
- ANNEX XVII - Montreal Cognitive Assessment Questionnaire
- ANNEX XVIII - Generalised Anxiety Disorder Assessment-7
- ANNEX XIX - Patient Health Questionnaire-9

## ANNEX I - Schedule of Assessments (SoA)

| Exam                                                                                 | Pre-treatment
(Clinic) | Treatment
(ICU) |                |                |                | Inpatient follow-up
(Ward)  | Outpatient follow-up
(Clinic) |
|--------------------------------------------------------------------------------------|---------------------------|--------------------|----------------|----------------|----------------|--------------------------------|----------------------------------|
| Study Days                                                                           | -D60 to D0                | D0                 | D1             | D2             | D3             | D4, D5, D6, D7, D8,
D9, D10 | D30                              |
| Informed Consent                                                                     | X                         |                    |                |                |                |                                |                                  |
| Cardiac surgery                                                                      |                           | X                  |                |                |                |                                |                                  |
| ICU Family Intervention                                                              |                           |                    | X              | X              | X              |                                |                                  |
| CAM-ICU and RASS                                                                     |                           | X                  | X              | X              | X              |                                |                                  |
| Vital Signs (Heart Rate, Blood Pressure, Respiratory Rate, Temperature, Saturations) | X             | X      | X  | X  | X  | X                  | X                    |
| Dyadic Interviews                                                                    |                           |                    |                |                | X  | X                  | X                    |
| Nursing interviews                                                                   |                           |                    |                |                | X  |                                |                                  |
| Montreal Cognitive Assessment                                                        |                           |                    |                |                |                | X                  | X                    |
| Generalised Anxiety Disorder Questionnaire-7                                         |                           |                    |                |                |                | X                  | X                    |
| Patient Health Questionnaire-9                                                       |                           |                    |                |                |                | X                  | X                    |
| CAM                                                                                  |                           |                    |                |                |                | X                  | X                    |

Vital signs to be collected at least one time during pre-treatment, inpatient follow-up, and outpatient follow-up stages; and daily highest/lowest vital signs during ICU stay.

Participants and family members/friends will be approached for dyadic interviews three times: day of ICU discharge, day of hospital discharge and up to one month post ICU discharge to discuss the intervention and assess delirium complications. Whether possible, interviews will be performed together, but single interview option will be provided.

Critical care nurses will be approached for one single interview to evaluate intervention acceptability, useability, and possible study limitations.

All quality-of-life questionnaires (QoL) are to be performed by participants one time during the inpatient stage and another time at the outpatient follow-up clinic appointment.

Short-term delirium outcomes post ICU discharge will be evaluated by performing daily CAM assessments during the inpatient period and once at the follow-up appointment.

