## **3. STUDY DESIGN**

The study will be conducted over twelve months in the Cardiac Intensive Care Unit at Hammersmith Hospital, Imperial College Healthcare NHS Trust. For this study, a total of 30 individuals (12 patients, 12 family members or close friends and 6 critical care nurses) will be recruited and interviewed to allow sufficient depth and richness of data. Patients and family members/friends will be mainly recruited from the ICHT pre-operative clinic outpatient department, which runs several pre-operative clinics per week. Each week, approximately eight patients undergo cardiac surgery, and the research team intends to recruit one patient and their family member/friend per a week for a period of 4 months.

All participants will be given time to consider their participation in the study and if happy will be consented by PI or other delegated member of the research team. Patients will be approached during one of their pre-operative clinic appointments and informed consent will be sought at this stage. Once written consent has been obtained, patients will be asked to nominate a family member or friend to be contacted by the PI. After signing the consent form, family members/friends will also be enrolled into the study and requested to self-record short videos pre-operatively (based on a guided script - ANNEX XIII), which will be safely uploaded to an iPad. In addition, patients will be requested to select multiple pictures, which will be securely uploaded into a digital photo frame. This package combination of videos and pictures will be shown to patients post-operatively in ICU. Critical care nurses will be recruited after they have provided direct care to at least one participant, who received the study intervention in ICU.

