This is a mixed methods research study including the collection of data from patient's medical notes, interviews and quality of life questionnaires in accordance with the schedule of assessments (SoA, Annex I). This study also involves the implementation of an auditory-visual sensory stimulation package in the cardiac ICU at ICHT to participants enrolled in the study. Digital photos will be shown continuously at the patient bedside after cardiac surgery and will always have reference to time and date. Additionally, videos will be played throughout participants' stay in ICU for at least three times per day and upon participant request. Videos will be also played when participant show signs of ICU delirium with the aim of reducing delirium incidence and improve overall better health outcomes. Simultaneously, primary outcomes measures (CAM-ICU, a routine delirium screening measure) will be collected by the research team, as this is evaluated twice a day as per usual standard of ICU practice, with the aim of assessing whether patients develop delirium during their stay in ICU.

Interviews with patients and families/friends will be held in three different occasions. The first one will be on the same day as ICU discharge, the second interview will be on the day of hospital discharge and the third one will be carried out up to a month following hospital discharge during their clinical follow-up appointment. Where possible, family members/friend and patient's interviews will be conducted together (dyadic interviewing), but the possibility of performing interviews separately will be given, so that participants feel able to discuss opinions freely without influence. Nurses' interviews will be held as a one-off and after they have provided direct care to participants who received the proposed intervention.

Each patient will be followed up daily on the wards and once at the monthly follow-up clinic up after ICU discharge, where cognitive and emotional assessments will be performed to evaluate delirium outcomes. The research team will also collect relevant information from participant's medical notes if any complications post ICU discharge arise during inpatient and follow-up stages.

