## **6. STUDY ASSESSMENTS**

### **6.1. ASSESSMENT AND FOLLOW UP**

#### **STUDY INTERVENTION**

The intervention will require family members/friends (selected by patients) to self-record short videos (during the preoperative stage) based on a carefully drafted guided script divided into two parts: a) Reorientation (discussing date/time/surroundings, family members on the video); b) Reassurance (providing comforting/supportive messages). Videos will be recorded either with a video-recorder device (provided by the research team) in the pre-operative clinic or at home using a personal smartphone. At a later stage, videos will be sent to an encrypted NHS email and securely uploaded in line with ICHT Information Governance to a password-protected iPad, which will also facilitate family-patient video calls in ICU. In addition, patients will be requested to select personal pictures pre-operatively, which will be also sent to the PI's encrypted NHS email and securely uploaded into a special digital photo frame with reference to time and date.

Digital photos will be shown continuously at the patient's bedside for 12 hours a day (between 8am to 8pm) and different family videos will be played three times at specific hours of the day (9am, 2pm and 7pm) throughout their stay in ICU. Additionally, videos will be also played upon patient request and last video shown that day will be re-played. In occasions when patients develop ICU delirium and considering personal consultee's agreement, the last video shown to participants will be re-played and patients will be closely monitored. This will help the research team to understand if the combination of personal pictures and family videos impacted patients' orientation and reassurance and if, ultimately, promoted the reduction of ICU delirium. The PI will be responsible for setting up the required equipment and delivering the intervention alongside ICU nurses as illustrated in the study diagram below (Annex XI).

The draft guided script of reorientation and reassurance messages was initially developed based on published research and considering patients' memories from their lived ICU experience(s) [15]. Subsequently, it was further refined within a lay focus group of patient and public members (with ICU lived experience) and reviewed by an expert panel comprising two critical

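### The delirium replay rule clashes with the video script: a replay between midnight and 9am tells the patient the wrong day and hour

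*Protocol*

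**What the plan says.** **Recording.** Family members or friends are "requested to self-record short videos pre-operatively" (section 3). Annex XIII sets out the content of each 3-minute video. In part A, Reorientation, the speaker mentions an approximate time (9am, 2pm or 6pm), the weekday and how many days have passed since the operation. In part B, Reassurance, the speaker explains that the message is recorded and adds supportive sentences. Section 6.1 and Annex XIII ask families to keep to the script's order.

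**Scheduled showings.** Annex I lists the programme as "ICU Family Intervention" in its ICU columns. Section 3: "videos will be played throughout participants' stay in ICU for at least three times per day". Section 6.1: "different family videos will be played three times at specific hours of the day (9am, 2pm and 7pm) throughout their stay in ICU". The photo frame, which carries the time and date, is shown "for 12 hours a day (between 8am to 8pm").

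**Replay on delirium.** Section 6.1: if the patient develops delirium and the personal consultee agrees, "the last video shown to participants will be re-played". Section 4.6 (Patients Regaining Consent) gives the same rule. The night-time checklist in Annex XII (8pm to 8am) asks at item 4 whether delirium developed overnight, at 4a whether the video was played again, and at 4b whether this improved the delirium.

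No readable part of the protocol says which video to use when the date has changed since the last showing.

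**The concern.** Each rule is reasonable alone, but together they produce a wrong message. A video that states a slot, a weekday and a postoperative day is correct only near that slot on that day. The replay rule selects a video by what was shown last, not by what is true now. After midnight, the last video belongs to the previous day.

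Two things are at stake. First, part A exists to reorient, and the replay goes to a patient who has just been found delirious. A wrong weekday, day count and hour is the opposite of what was intended. Second, checklist item 4b asks whether the replay helped. If replays after midnight carry a wrong cue, a poor answer there may reflect the replay rule and not the intervention. That matters in a 12-patient study whose purpose is to judge whether the intervention is workable.

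**Working it through.** The protocol states no figure on this point, so there is nothing to reproduce. The check is a reading of the text plus clock arithmetic.

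**Inputs**
- Scheduled showings: 9am, 2pm, 7pm (section 6.1).
- Spoken evening time: 6pm (Annex XIII, part A).
- Replay rule: the last video shown (sections 4.6 and 6.1).
- Night checklist window: 8pm to 8am (Annex XII, Table 2).

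**Step 1: which video is last.** From 7pm until 9am, which is 14 hours, the last scheduled video is the evening one. If the 7pm showing was missed, the last video is an earlier one from the same day, so the argument is unchanged.

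**Step 2: what it says when replayed**

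| Replay time | Weekday | Day count | Age of the stated 6pm |
|---|---|---|---|
| 8pm | correct | correct | 2 h |
| Just before midnight | correct | correct | almost 6 h |
| Midnight | previous day | one too low | 6 h |
| 3am | previous day | one too low | 9 h |
| Just before 9am | previous day | one too low | almost 15 h |

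The wrong-day window is midnight to 9am, or 9 hours. Of the 12-hour night checklist window, 8 hours fall after midnight. The window does not arise on the first night if no video has yet been shown.

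**Step 3: evening slot.** 7pm − 6pm = 1 hour, in one of the three daily showings.

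**Step 4: could it occur in 12 patients?** The protocol does not give the frequency of delirium after midnight. Let p be the delirium incidence (section 1.1 gives 30–80% for ICU generally and up to 55% after cardiac surgery). Let f be the share of patients with delirium who get a replay after midnight; f is my assumption. Treating patients as independent, the expected number affected is 12·p·f, and the chance of at least one is 1 − (1 − p·f)^12.

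- p = 0.30, f = 0.10: expected 12 × 0.03 = 0.36; chance 1 − 0.97^12 = 0.31.
- p = 0.55, f = 0.25: expected 12 × 0.1375 = 1.65; chance 1 − 0.8625^12 = 0.83.
- p = 0.80, f = 0.50: expected 12 × 0.40 = 4.8; chance 1 − 0.60^12 = 0.998.

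The range is wide because f is unknown. It shows only that the case could well arise in this sample.

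**The case against.** The best reply is that this is a small practicality of the kind a feasibility study exists to find. The script was co-produced with people who have ICU experience and was reviewed by an expert panel. Its times are only approximate, part B says the message is recorded, and patients are closely monitored after a replay. Nurse interviews cover limitations. No sample size or analysis depends on the point.

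Much of this stands. It makes the 6pm/7pm mismatch minor and softens the overnight cue. It does not make yesterday's weekday or day count correct, and the error is foreseeable now at almost no cost.

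A reader might infer more than the text supports:

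- **That Annex I stops the videos, or delirium screening, at D3.** The rows "ICU Family Intervention" and "CAM-ICU and RASS" are marked only to D3, but D0 to D3 sit under an ICU heading and D4 to D10 under a ward heading. Footnote 1 speaks of "daily highest/lowest vital signs during ICU stay", sections 3 and 6.1 cover the whole ICU stay, and section 8.4 deletes the videos at ICU discharge. D3 reads as a nominal end of stay.
- **That long-stay patients run out of valid videos.** If exactly nine were recorded (3 × 3 for D1 to D3), a stay to D5 would leave 15 − 9 = 6 of 15 showings unmatched, and a stay to D7 would leave 21 − 9 = 12 of 21. This is illustration only: neither the number of videos nor the length of stay is given, and the delivery diagram in Annex XI is not shown.
- **That 9/24 = 37.5% of replays are wrong.** That is a share of clock hours, not of replays.
- **That overnight replays distort the count of delivered showings.** Daytime checklist item 3 covers scheduled daytime delivery. Overnight replays are recorded separately at item 4a.
- **That nothing else shows the time at night.** Section 6.1 limits the photo display to 8am to 8pm, but no passage says that the frame's clock is dark outside those hours.

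**Conclusion.** The point holds in a limited form. Once videos have begun, the stated replay rule, applied to videos made to the stated script, gives a delirious patient the wrong weekday, a day count one too low and an evening hour whenever the replay falls between midnight and the 9am showing. This follows from the text. It assumes only that families follow the script and nurses follow the replay rule. Between 8pm and midnight the day is right and only the hour is stale. The 6pm/7pm mismatch is a separate, minor inconsistency.

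The frequency is unknown, and no estimate or sample size is affected. It is still more than a missing detail, because following the protocol as written produces a cue contrary to the purpose of part A. It should be corrected.

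**What to change.** 1. In sections 4.6 and 6.1, add a clause: for a delirium replay between midnight and the 9am showing, play one day-neutral video (no clock time, weekday or day count), or only the part B segment of the last video. The nurse states the current day and time. Otherwise keep the last-video rule.
2. Add the day-neutral video, about 3 minutes, to Annex XIII. Use it also on any ICU day for which no day-specific video was recorded.
3. In Annex XIII, change 6pm to 7pm so that the script matches section 6.1.

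**Cost.** One clause in each of two sections, a short addition and one changed time in Annex XIII, and at most one extra 3-minute recording per family (none if part B alone is used). The downside is that the night replay then carries no recorded time cue, so orientation depends on the nurse saying the day and time. Sample size, assessments and analysis are unchanged.
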